## **2.3 Project design**

Prospective experimental multimodal (clinical, biomechanical, biological) data collection with block randomization and cross-over.

We will recruit equal numbers of male and female subjects in each group. Conditions will be block randomized in two blocks of possible condition orders per sex per subject group to prevent a potential systematic condition effect. Blinding to the experimental condition is not possible because of the obvious differences between conditions (partial weight bearing and additional load). However, the person processing the data will be blinded to the condition. Because it does not seem feasible that a subject can actively alter the load-induced changes in blood markers of articular cartilage, it is assumed that this approach is appropriate for answering the research questions.

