## **3 PROJECT POPULATION AND STUDY PROCEDURES**

### **3.1 Project population, inclusion and exclusion criteria**

We will examine a cohort of 96 subjects. Experiments for all sub aims will involve the same subjects (N=24 per group):

- Group 1: healthy subjects aged between 20 and 30 years
- Group 2: subjects with previous ACL injury aged between 20 and 30 years
- Group 3: healthy subjects aged between 40 and 60 years
- Group 4: subjects with previous ACL injury aged between 40 and 60 years

A minimum age of 20 years and maximum age of 60 years was chose to ensure skeletal maturity and to include an age range with increased risk of early knee OA (above 40 years).

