2. We will investigate the effect of age on the slope for each outcome by a mixed model with intercept, load, age and the interaction between age and load as fixed effects and intercept and load as random effects.
3. We will investigate the effect of tissue and inflammation status (in addition to age) on the slope by a mixed model with intercept, load, age, tissue status, inflammation status and the interaction between the load and age, tissue status and inflammation status, respectively, as fixed effects and intercept and load as random effects. In dependence of the correlation between T2 relaxation time and cartilage thickness we will fit a separate model for both aspects of tissue status or a joint model.
4. We will investigate the correlation between the slopes for the two outcomes by corresponding joint mixed models and investigate also a dependence of the correlation on age, tissue status and inflammation status.
5. We will investigate the correlation of the slopes across the five different biomarkers by corresponding joint mixed models.

To allow simple comparisons of effects across the different biomarkers we will rescale all biomarkers to a median level of 100 at  $t_0$  under 100% intended ambulatory load. The dependence of the slope on age, tissue status and inflammation status will be expressed as the expected slope at selected values, e.g. lower and upper 10% population percentiles. The value of these factors will be depicted by the explained biological variation. To take the joint investigation of five – however probably correlated – biomarkers into account, we will use a reduced significance level of 0.025. Further explanatory and hypotheses generating analyses are planned with respect to new definitions of potential markers (e.g. ratios between two markers) or alternative definition of explaining factors (e.g. the three single inflammation markers).

With respect to the secondary objective, we will make use of additional clinical outcomes measured both a baseline and at the 2-years follow up. The primary outcome will be the change in T2 relaxation time. Secondary outcomes are the kinematics and kinetics in the initial gait analysis and single leg hop, the change in cartilage thickness, KOOS score, modified KSS score and physical activity. The distribution of the outcomes will be depicted in an initial data analysis. The research questions will be addressed by the following sequence of analyses:

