1. We will investigate for each biomarker the associations of the individual slope with the clinical outcomes by a corresponding regression model focusing on effect sizes and explained variation.
2. We will investigate the independent prognostic value of the individual slopes for each biomarker by corresponding adjustments, first for age and then also for tissue status and inflammation.
3. We will investigate a potential effect modification by physical activity by adding corresponding interactions terms to the regression models.
4. In case the individual slopes do not carry independent prognostic value, we will investigate their mediation effects on the path from age (or age, tissue status and inflammation) towards the clinical outcome.
5. In case of independent prognostic value of the individual slopes for several biomarkers, we will also consider the amount of independent prognostic information by considering a model with all these biomarkers as covariates.

In all regression models the baseline value of the clinical outcome will be included as covariate. Since the individual slopes are estimated and we can assess their standard error, we will correct for this measurement error using regression calibration.

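### The cross-over models omit test day, and the prognostic models omit ACL status: a possible loss of precision in the first case and residual confounding in the second

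*Protocol*

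**What the plan says.** Section 2.3 describes a cross-over over three test days: "Conditions will be block randomized in two blocks of possible condition orders per sex per subject group". It also fixes the sex ratio: "We will recruit equal numbers of male and female subjects in each group". Section 3.1 sets four groups by age band and ACL history ("Experiments for all sub aims will involve the same subjects (N=24 per group"), for example "Group 2: subjects with previous ACL injury aged between 20 and 30 years". Of the 96 subjects, 48 therefore have a previous ACL rupture.

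Section 4.1 then fixes the models. Primary step 1 has intercept and load, both fixed and random. Step 2 is a "mixed model with intercept, load, age and the interaction between age and load as fixed effects and intercept and load as random effects". Step 3 is a "mixed model with intercept, load, age, tissue status, inflammation status and the interaction between the load and age, tissue status and inflammation status", with the same random effects. For the secondary objective, step 2 judges whether the individual slope has independent prognostic value "by corresponding adjustments, first for age and then also for tissue status and inflammation". A closing sentence adds the baseline value of the clinical outcome to every regression, and step 3 adds interactions with physical activity.

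Test day, condition order, sex and ACL status are in none of these models. Under Subject characteristics in section 4.1, sex and the ACL details serve to describe the groups.

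**The concern.** The two omissions differ in kind.

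**Test day.** The design balances condition order over the three days, but the models do not use that balance. A trend shared by all subjects from day I to day III (habituation to the treadmill or the harness, for instance) then counts as residual noise in each subject's slope. Each slope rests on only three conditions, so residual noise matters.

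**ACL status.** The protocol itself supplies both arms of a common cause. Section 2.1 expects mechanosensitivity to change after injury. The sample size section expects a wider spread of slopes partly because injured and healthy subjects are both included. Section 3.3 i) says T2 is raised after ACL injury, and section 2.1 names ACL treatment and rehabilitation factors as possible influences on the slope–degeneration relation. A slope that partly marks injured versus uninjured knees could therefore appear to predict T2 change beyond age, tissue status and inflammation.

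**Working it through.** **Inputs from the protocol.** N = 96; 10% drop-out, so n = 86; significance level 0.025; slope SDs 3.7, 7.4 and 11.1; standard errors 1.87, 1.27 and 1.24 from the first simulation; stated powers 71%, 85% and 89% (primary) and 72% and 95% (secondary). The protocol gives no size for a day trend, a sex effect or an ACL effect. Those are assumptions below.

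**Step 1: reproduce the plan's figures.** Power = Φ(√(n−3)·atanh(r) − 2.241), where 2.241 is the two-sided 0.025 critical value.
- n = 86, r = 0.3: 71.9% (stated 72%).
- n = 86, r = 0.4: 94.7% (stated 95%).

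For the primary objective, the sampling variance v of a slope can be backed out of the first simulation through SE(SD) ≈ (s² + v)/(2s)·√(2/95). At s = 7.4: v = 1.27·14.8/0.1451 − 54.76 = 74.8. The other two SDs give 81.7 and 66.5, so take v = 75. With r = √(p·s²/(s² + v)) and N = 96, where p is the share of slope variance explained:
- s = 3.7, p = 50%: r = 0.278, power 70% (stated 71%).
- s = 7.4, p = 25%: r = 0.325, power 84% (stated 85%).
- s = 11.1, p = 20%: r = 0.353, power 90.5% (stated 89%).

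The approximation is good enough to show differences.

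**Step 2: balance of order.** Three conditions have 6 orders. 6 orders × 2 blocks = 12 per sex per group, and 12 × 2 sexes × 4 groups = 96. Averaged over the six orders, a linear day trend contributes zero to the mean load slope. It does add variance: a drift of one residual SD from day I to day III adds 0.125 to a slope sampling variance of 0.5, that is 25%.

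**Step 3: gain from fitting test day (assumed shares of residual variance).**

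| Scenario | 0% | 10% (v = 67.5) | 20% (v = 60) |
|---|---|---|---|
| s = 3.7, p = 50% | 70% | 74% | 79% |
| s = 7.4, p = 25% | 84% | 87% | 89% |

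The 20% column needs 15/60 = 25% extra variance, which is the one-SD drift of step 2. The 10% column needs 7.5/67.5 = 11%, a drift of √(0.111/0.25) ≈ 0.67 residual SD.

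**Step 4: sex.** If sex × load explains 2–10% of slope variance, fitting it adds at most about 2 power points.

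**Step 5: ACL status in the prognostic test.** Suppose slope and T2 change are unrelated given ACL status. If ACL explains a share q of each beyond the listed covariates, the spurious partial correlation is √(q·q) = q. With n = 86 and two-sided 0.025:
- q = 10%: declared significant 9% of the time with error-free slopes, 5% at slope reliability 0.45.
- q = 20%: 35% and 16%.

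Reliability here is s²/(s² + v); with v = 75 it is 0.15, 0.42 and 0.62 at the three slope SDs, so 0.45 is a mid-range assumption.

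The planned covariates can also be put in the model. The simulation takes n = 86, error-free slopes, and tissue status and inflammation themselves shifted 0.5–0.8 SD by ACL injury. It adjusts for age, tissue status and inflammation:

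| ACL effect on slope and on T2 change (assumed) | False positives, planned model | With ACL status added |
|---|---|---|
| 0.5 SD | about 3–5% | about 2–3% |
| 0.8 SD | about 10–14% | about 2–3% |
| 1.0 SD | about 22–28% | about 2–3% |

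**Step 6: cost.** Replacing n − 3 by n − 3 − k for k = 1, 2, 3 added covariates lowers the 71.9% to 71.3%, 70.7% and 70.1%. This reads 0.3 as the correlation that remains after adjustment.

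**The case against.** Much can be said for the plan.

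- **Test day.** Order is balanced, the outcome is normalised to the same day's pre-walk sample, all of a subject's samples share a plate, and testing follows 24 hours without physical activity, at a fixed time of day, after an hour seated. A day term removes only a trend common to everyone, not a subject's own day-to-day noise. All of this stands: the gain may be small or nil. A reader might infer from the omission that the slopes or the age effect are biased. The design does not support that, because an additive day effect averages out over complete blocks.
- **Sex.** A reader might infer that a blocking factor must appear in the model. Load varies within subject, a sex main effect is taken up by the random intercept, and sex is equal in every group. The possible gain is negligible.
- **ACL status as an unadjusted confounder.** That reading is too strong. Baseline T2, thickness, IL-6 and the baseline outcome all carry part of the injury effect. What remains is residual confounding.
- **ACL status in the primary models.** Injury lies upstream of tissue status and inflammation, and recruiting on it helps create the contrasts that Hypotheses 1.2 and 1.3 test. ACL × load as a standard term would compete with them. This stands.
- **Scope.** Such terms are often settled in a separate analysis plan. Here, however, section 4.1 states the fixed effects and the adjustment set outright, so these are stated choices.
- **Size.** The larger false-positive rates need large ACL effects on both variables and slopes without error. This stands too.

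**Conclusion.** The point holds as a worthwhile, inexpensive improvement in two places.

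The cross-over models should use the period structure that the design provides. The benefit is precision alone: 0 to about 9 power points in the weakest primary scenario for day shares of 0–20%, all assumed.

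The claim of prognostic value independent of age, tissue status and inflammation should be tested with ACL status in the model. The cohort is split on it by design, and the protocol gives reasons to expect an effect on both slope and cartilage. The inflation is slight at 0.5 SD (about 3–5% against 2.5%) and serious only at 0.8–1.0 SD (about 10–14% and 22–28%), in each case with error-free slopes. Measurement error in the slopes lowers these rates. The protocol gives no ACL effect size, so nothing here shows that a spurious association will occur, only that the planned model could not tell it from a true one.

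**What to change.** 1. Add test day (I, II, III) as a categorical fixed effect in primary steps 1–3.
2. Add ACL status to the adjustment set in secondary step 2.
3. Report primary step 3 a second time with ACL status and ACL × load, labelled as a sensitivity analysis, so that the tissue-status and inflammation contrasts can be read with and without it.
4. Sex and sex × load are optional.

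Every variable is already recorded. Test day costs two degrees of freedom in the mixed models. One to three extra covariates in the prognostic regression lower power at r = 0.3 from 72% to about 70–71%. In the sensitivity analysis, intervals for tissue status and inflammation will be somewhat wider.

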- **Hypothesis 2.3:** The slope of the relationship between ambulatory load and mechanosensitive blood markers of articular cartilage correlates with the change in Knee Injury and Osteoarthritis Outcome Score (KOOS) and modified Knee Society Score (KSS).
- **Hypothesis 2.4:** Weekly physical activity levels influence the associations postulated in Hypotheses 2.1, 2.2 and 2.3.

We expect that altered mechanosensitivity will lead to articular cartilage degeneration measured as articular cartilage thinning and decrease in articular cartilage quality and that physical activity level modulates this relationship. Other potential influencing factors in patients with anterior cruciate ligament (ACL) injury include treatment (conservative or operative), time of operation (if applicable), duration of physiotherapy, time of return to work, time of return to sport, or type of sports before injury.

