### Secondary endpoints

- Change in T2 relaxation time and cartilage thickness from baseline to follow-up
- Score in questionnaires: Modified KSS and the KOOS
- Change in modified KSS and KOOS scores within the 2 years
- Age, bodyweight (BW) sex of the subject
- Inflammation status at baseline and at 24-month follow-up (IL-6)
- Resting blood biomarker concentration at 24-month follow up
- Physical activity (PA) level during 7 days after the baseline (prior to the experiment), during the experiment and during 7 days after the follow-up measurement.
- Ambulatory load at each condition (maximum vertical ground reaction force (GRF) and total vertical ground reaction impulse during walking)
- Number of steps taken during the test day
- Joint kinematics for the three loading conditions (dynamic range of motion during walking at the ankle, knee and hip)
- Joint kinematics for the normal load condition, running and single leg hops (rotational offset and difference in maximum knee moment between injured and not injured knee)
- Heart rate during and after the walking stress test
- Tissue status at baseline: T2 relaxation time and cartilage thickness

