Fig. 2: **Prospective design for assessing cartilage degeneration.** At baseline, a clinical exam, bilateral knee MRI, gait analysis, physical activity level and a walking stress test will be conducted. The dose-response relationship determined in the walking stress test at baseline will be related to changes in articular cartilage thickness and quality from baseline to the 24-month follow-up. The 12-month follow-up serves as additional endpoint to stay in contact with the participants thus minimizing drop-outs.

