### **4.2. Handling of missing data**

All data will be checked for quality and completeness at the time of testing. Hence, we do not expect missing data due to technical difficulties. Blood samples will be taken at specific time points. Complicacy during blood sampling and delayed draw times will be registered in the study protocol. To minimize drop-out before completion of the 3 test days, we will inform the participants in detail about the duration and content of each session. To prevent logistical time problems, we will set all appointments prior to the clinical assessment. Incomplete data sets will be included in the statistical analysis. Missing values will be replaced by the mean. Recruitment will be continued until 24 participants per group completed the baseline assessment and all three walking stress test days to ensure complete data sets for addressing the primary objective.

To minimize the drop-out rate during the 24-month follow-up for answering the secondary objective, we will contact the participants at 12-months as intermediate clinical follow-up (KOOS only). We will account for drop-outs by performing intent to treat analyses.

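### The 12-month KOOS has no place in the analysis, and a missing 24-month KOOS would be filled with the mean even when the subject's 12-month score is known

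*Protocol*

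**What the plan says.** KOOS change is one of the protocol's hypotheses. Under Hypothesis 2.3 (section 2.1) the slope "correlates with the change in Knee Injury and Osteoarthritis Outcome Score (KOOS) and modified Knee Society Score (KSS". Section 2.2 lists the endpoint as "Change in modified KSS and KOOS scores within the 2 years".

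KOOS is collected at baseline, at 24 months and once in between. Section 4.2 says that "we will contact the participants at 12-months as intermediate clinical follow-up (KOOS only", and the Figure 2 caption in section 3.3 says: "The 12-month follow-up serves as additional endpoint to stay in contact with the participants thus minimizing drop-outs".

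The analysis in section 4.1 names two time points: "we will make use of additional clinical outcomes measured both a baseline and at the 2-years follow up". Its leading outcome is not KOOS: "The primary outcome will be the change in T2 relaxation time". KOOS is among the secondary outcomes. The models are regressions on the individual slope: "In all regression models the baseline value of the clinical outcome will be included as covariate". None contains a 12-month value or a repeated-measures term.

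On incomplete data, section 4.2 says that incomplete data sets enter the analysis and that "Missing values will be replaced by the mean". It adds that drop-out by 24 months will be met by intention-to-treat analyses and gives no method. Section 3.4 says that data collected before withdrawal or discontinuation will be kept in later analyses, to guard against bias.

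**The concern.** For a subject lost between 12 and 24 months, the 12-month KOOS is the closest observation to the missing endpoint. The stated method has no route for it. The baseline-adjusted 24-month regression cannot take it in, and the only concrete rule for a missing value substitutes a mean that ignores both the subject's own course and the subject's slope. That does not deliver what section 3.4 promises.

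At stake is the size of the slope-KOOS association. Section 4.1 says these regressions focus on effect sizes and explained variation, and those are the quantities that mean replacement shrinks. If subjects who are doing badly at 12 months are the ones who leave, some further shrinkage arises, which the 12-month value could remove.

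**Working it through.** **Inputs from the protocol:** 96 subjects (section 3.1); 10% drop-out, and power of 72% at a correlation of 0.3 and 95% at 0.4 (section 4.1, sample size); significance level 0.025 (section 4.1, given for the primary objective).

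**Assumptions, not in the protocol:** true standardised slope effect 0.30 at 24 months and 0.15 at 12 months; correlation rho between 12- and 24-month KOOS of 0.5 to 0.7; 12-month KOOS complete; all loss after 12 months. KOOS values are treated as already adjusted for baseline.

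**Step 1: the plan's own power.** Power = Φ(atanh(r)·√(n − 3) − z), with n = 96 × 0.9 = 86.4, taken as 87, and z = 2.241 (two-sided 0.025).
- r = 0.3: 0.3095 × 9.165 − 2.241 = 0.595, so 72.4%.
- r = 0.4: 0.4236 × 9.165 − 2.241 = 1.641, so 95.0%.

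Both stated figures are reproduced. They already allow for losing 10% of subjects at 24 months.

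**Step 2: mean replacement by formula.** With a share m missing at random, the filled-in subjects add nothing to the covariance between slope and KOOS but still count in the variance of the slope. The coefficient is therefore multiplied by (1 − m): 0.30 × 0.9 = 0.27. The outcome variance also falls to 0.9, so the correlation becomes 0.27/√0.9 = 0.285 and the explained variation falls from 9% to 0.285² = 8.1%.

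**Step 3: simulation.** 96 subjects, 4,000 repetitions, 10% drop-out. In the second mechanism the log-odds of drop-out rise by 1.5 per SD of worse 12-month KOOS. The likelihood estimate combines two regressions: 12-month KOOS on slope in all subjects, and 24-month KOOS on slope and 12-month KOOS in completers. Cells show the mean estimate (empirical SD).

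| Drop-out | rho | Mean replacement | Complete cases | Likelihood with 12-month KOOS |
|---|---|---|---|---|
| Random | 0.5 | 0.269 (0.096) | 0.299 (0.106) | 0.299 (0.105) |
| Random | 0.7 | 0.269 (0.096) | 0.299 (0.106) | 0.299 (0.103) |
| Depends on 12-month KOOS | 0.5 | 0.261 (0.094) | 0.291 (0.103) | 0.299 (0.104) |
| Depends on 12-month KOOS | 0.7 | 0.258 (0.090) | 0.288 (0.099) | 0.299 (0.099) |

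The smaller spread under mean replacement is not a gain in precision. It is the complete-case spread multiplied by the same factor: 0.106 × 0.9 = 0.095.

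**Step 4: what the 12-month value adds to precision.** Under random drop-out the SE ratio of complete cases to the likelihood model is 1/√(1 − m·rho²).
- rho = 0.5: 1/√0.975 = 1.013, so the SE is about 1.3% lower.
- rho = 0.7: 1/√0.951 = 1.025, so the SE is about 2.5% lower.

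Under drop-out that depends on 12-month KOOS, the simulated spreads of the two methods are practically equal.

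**Step 5: split of the gain.** Under random drop-out, the whole recovery of 0.03 comes from not using mean replacement. Under KOOS-dependent drop-out, about 0.03 of the 0.04 comes from that and about 0.01 from using the 12-month score.

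**The case against.** The strongest reply is that the plan is coherent as it stands. The endpoint is the 2-year change, the 12-month contact exists mainly to keep participants in the study, and a baseline-adjusted 24-month regression is a legitimate analysis of that endpoint. This stands: there is no error in taking 24 months as the target.

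A reader might infer that the 12-month KOOS is discarded. The protocol does not say so. Sections 3.4 and 4.2 say that early and incomplete data are included. What can be said is that no method of use is stated, and that the stated methods leave no room for one. This is more than a detail left to a separate analysis plan, because section 4.1 fixes the time points and the model type and section 4.2 fixes the filling rule.

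A reader might also infer a substantial loss of precision. At 10% drop-out the gain over complete cases is 1 to 3% of the SE at most. Averaging the effect over 12 and 24 months would look more precise, but that is a different quantity which the protocol does not define.

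The mean-replacement sentence stands in the paragraph about the test days, and the follow-up paragraph speaks only of intention to treat. One could argue that the rule was never meant for 24-month KOOS. It is written without any limit, however, and no other rule is given. If it were not applied and complete cases were used, the bias would range from none to about 0.01.

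Bias beyond the effect of mean replacement needs drop-out that depends on the 12-month KOOS, and the protocol gives no evidence on that. Subjects lost before 12 months gain nothing.

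**Conclusion.** The point holds as a minor one. The protocol collects a 12-month KOOS, calls the contact an endpoint, and gives the value no use. As written, it would replace a missing 24-month KOOS by the mean even when the subject's 12-month score is on file, which sits badly with section 3.4.

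Under the stated assumptions the association shrinks from 0.30 to about 0.27 under random drop-out and to about 0.26 if drop-out depends on the 12-month KOOS. A shift of 0.03 is about 0.28 of a standard error (0.03/0.106). It is modest but systematic, and avoidable. Most of it comes from mean replacement; the 12-month score adds about 0.01 and little precision.

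The documents do not support a wider claim. Change in T2, the leading outcome of this objective, has no 12-month value and gains nothing from the 12-month contact. The same is true of cartilage thickness and the modified KSS.

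**What to change.** In section 4.1, analyse KOOS with a likelihood-based repeated-measures model of the 12- and 24-month values. Include slope, visit, slope-by-visit interaction, baseline KOOS and the adjustments already planned. Declare the 24-month slope effect the main result, so that the 2-year endpoint in section 2.2 is unchanged, and report the 12-month effect beside it. State in section 4.2 that mean replacement is not applied to KOOS. Multiple imputation of the 24-month KOOS that uses the 12-month value is an acceptable equivalent. Name the 12-month KOOS in section 2.2 so that it agrees with the Figure 2 caption.

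The cost is modest extra analysis work, mainly carrying the planned regression calibration for the estimated slopes, and the physical-activity interactions, into this model for KOOS. No new visit or measurement is needed.

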### **Sample size calculation**

To judge the adequacy of the intended samples sizes, we performed simulation studies using the estimated population means, the estimated populations standard deviations (recently published for COMP), and the estimated residual variance as true parameter values and assuming a correlation of 0.8 between intercept and slope. We then varied the population standard deviation of the slope by factors of 2 and 3 because we expect in our study a substantially larger population variation due to wider age range and including both diseased and healthy subjects. We conducted four simulation studies corresponding to the intended main analyses. All simulation studies are based on the planned sample size of 96 subjects and include 2500 repetitions per simulation.

With respect to *the primary objective*, the first simulation study looked at the standard error of the estimates of the population standard deviation of the slope. We observed standard errors of 1.87, 1.27, and 1.24 for population standard deviations of the slope of 3.7, 7.4 and 11.1, respectively. This suggests that we can obtain a rather precise picture of the population variation.

In the second simulation, we looked at the power to demonstrate a significant interaction between load and a single normally distributed covariate that can explain some of the biological variation of the slope. Already for a population standard deviation of 3.7, we obtained a power of 71% if the covariate can explain 50% of the biological variation. For a population standard deviation of 7.4, we reached a power of 85% if the covariate can explain at least 25% of the variation. For a population standard deviation of 11.1, we obtained a power of 89% if the covariate can explain at least 20% of the variation.

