In the third simulation we considered the case of three normally distributed covariates with a correlation of 0.3, equal interaction terms with the load, and explaining together a certain percentage of the biological variation. We assumed here a moderate correlation of 0.3 to take into account that tissue status and inflammation status are both probably related to age and to each other. Our interest was the power to demonstrate a significant interaction with the load for one a priori selected covariate if the covariates together can indeed explain a large amount of a substantial population variation. For a population standard deviation of 7.4, we reached a power of 70% if the covariates explain together at least 82% of the variation, and for a population standard deviation of 11.1 we reach a power of 80% if they explain together 74% of the variation. This suggests that we will be able to demonstrate interactions between tissue status/inflammation status and ambulatory load on top of the interaction with age if the interactions are of similar magnitude as those for age, if all three factors explain a substantial amount of the biological variation, and if we have a substantial population variation of the slope.

With respect to the secondary objective, we can use standard formulas to determine the power to demonstrate a significant association in dependence on the true correlation between the individual slopes and a clinical outcome. They indicate that we have a power of 72% to find a significant association if the true correlation is 0.3, and a power of 95% if the true correlation is 0.4, taking into account a potential drop out rate of 10%. With respect to the ability of assessing an independent prognostic value, we performed a simulation study taking up the scenario of the third simulation study above, but now focusing on the situation where age, tissue status and inflammation can explain the variation in the individual slopes only to a smaller degree of 40%. If we further assume that these three variables together can explain the variation in the clinical outcome to the same degree as the individual slopes, we obtain a power of 80% to demonstrate an independent prognostic value if the individual slopes have a partial correlation of 0.6 with the outcome.

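### Joint prognostic information is measured only for biomarkers that already looked prognostic in the same participants, so ordinary explained variation is likely to be too high when true effects are modest

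*Protocol*

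**What the plan says.** Protocol section 4.1 lists five steps for the secondary objective.

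- Step 1 relates each biomarker's individual slope to the clinical outcomes by regression, "focusing on effect sizes and explained variation".
- Step 2 asks whether each slope has prognostic value independent of age, and then also of tissue status and inflammation.
- Step 5 is conditional on several biomarkers showing such independent value. In that case "we will also consider the amount of independent prognostic information by considering a model with all these biomarkers as covariates". "These" refers to the biomarkers that met the condition.

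All models include the baseline value of the outcome, and error in the estimated slopes is to be handled by regression calibration. No other correction is described.

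The analysis concerns five biomarkers ("We will investigate the correlation of the slopes across the five different biomarkers by corresponding joint mixed models"), which the protocol expects to be correlated, without saying how strongly. Under the primary objective it states "we will use a reduced significance level of 0.025".

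The sample size section says "All simulation studies are based on the planned sample size of 96 subjects". For the secondary objective it gives "a power of 72% to find a significant association if the true correlation is 0.3". At a correlation of 0.4 the stated figure is 95%. Both allow for losing one participant in ten. For independent prognostic value it gives 80% power at a partial correlation of 0.6.

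**The concern.** Step 5 fixes the order of work: choose biomarkers by their result, then measure how much the chosen ones explain, using the same people. A biomarker that passes because chance pushed its estimate upwards carries that chance into the joint model, so the in-sample explained variation of the selected set tends to exceed what the same set would explain in new participants. Regression calibration does not remove this, because it corrects for imprecision in each person's slope and not for the choice of slopes.

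Prognostic ability is the secondary objective, and section 1 presents the study as proof-of-concept for a possible diagnostic test. A combined explained-variation figure could well be carried into later work, so it should not be inflated by the way it was obtained.

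**Working it through.** **Inputs from the protocol.** Planned N = 96; dropout 10%, so 96 × 0.9 = 86.4, about 86 (derived, not printed); five biomarkers; significance level 0.025; planning correlations 0.3 and 0.4, and partial correlation 0.6 for independent value.

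**Assumptions not in the protocol.** The pass criterion is p < 0.025, two-sided. The five slopes have equal partial correlation r with the outcome and equal mutual correlation ρ between 0 and 0.7. Slopes are free of measurement error. Five adjusting covariates are used (age, two tissue measures, inflammation, baseline outcome).

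**1. Reproducing the plan's own figures.** Power = Φ(atanh(r)·√(n−3) − z), with n = 86 and z = 2.241 for two-sided 0.025.

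- r = 0.3: 0.3095 × 9.110 = 2.820; 2.820 − 2.241 = 0.579; Φ = 71.9% (stated 72%).
- r = 0.4: 0.4236 × 9.110 = 3.860; 3.860 − 2.241 = 1.618; Φ = 94.7% (stated 95%).

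Two-sided 0.05 would give 80.5% and 97.1%, and N = 96 without dropout 77.1% and 96.7%. The stated power therefore fits n = 86 and two-sided 0.025, which supports those inputs.

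**2. Height of the gate.** The smallest observed correlation that reaches significance is about tanh(2.241/9.110) = tanh(0.246) = 0.24. A biomarker with a true r of 0.2 passes only when chance has raised its estimate.

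**3. Simulation of steps 2 and 5.** In each simulated trial the slopes passing the test are selected. If at least two pass, they are fitted jointly in the same data. The mean in-sample partial R² is compared with the mean true partial R² of the same sets, which for q slopes is q·r² / (1 + (q−1)·ρ).

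| True r | In-sample R² ÷ true R² of the selected set |
|---|---|
| 0.2 | 2.3 to 2.8 |
| 0.3 | 1.3 to 1.6 |
| 0.4 | 1.0 to 1.2 |
| 0.6 (ρ 0.3 to 0.7 only) | 1.01 to 1.06 |

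At r = 0.6, ρ = 0 is impossible, because 5 × 0.36 = 1.8 exceeds 1.

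Example at r = 0.2, ρ = 0.3: in-sample R² 0.182 against true 0.071, a ratio of about 2.5. Step 5 is reached in 48% of trials.

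**4. How much is selection and how much is overfitting.** With all five slopes fixed in advance, plain R² is still 1.2 to 2.1 times the true value at r = 0.2 and 1.06 to 1.46 times at r = 0.3, so part of the gap is ordinary overfitting. Adjusted R² removes that part but not the selection: after selection it is still about 1.8 to 2.1 times too high at r = 0.2. Adjusted R² from the fixed five-slope model is 0.93 to 1.03 times the true value at every setting tried.

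**5. A different target.** Compared with the true R² of all five biomarkers, the selected model's plain R² at r = 0.2 is 1.1 times (ρ = 0) to 2.7 times (ρ = 0.7). With uncorrelated slopes and r from 0.25 to 0.4 it is 0.91 to 0.98, slightly too low.

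**The case against.** The strongest reply is that a protocol commonly leaves shrinkage, adjusted R² and bootstrap to the statistical analysis plan, which is not shown, and that nothing here rules them out. That stands as far as the missing correction goes. It does not remove the point, because the protocol itself sets the rule that only biomarkers found prognostic enter the joint model.

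A reader might infer that the protocol commits to reporting plain explained variation from step 5. It does not. That measure is named in step 1, whose single-marker results cover every biomarker and are unselected. Step 5 names no measure, and no p-value criterion is given for entering it.

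A reader might also infer that the figure will be about doubled. Twofold holds only near a true partial correlation of 0.2, which is weaker than the protocol's planning values. At 0.3 and 0.4 the overstatement is modest or small, and at 0.6, the value used for independent prognostic value, it is negligible. It can be argued that error in the slopes makes nominal correlations act like smaller ones, but the protocol does not give the figures to settle that.

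The choice of target matters too. Against all five uncorrelated biomarkers there is little or no overstatement. This reply is weaker here, since the protocol expects correlated biomarkers.

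Finally, step 5 comes last, is conditional, and corresponds to none of hypotheses 2.1 to 2.4. That limits the importance of the point.

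**Conclusion.** The point holds in limited form. Step 5 selects biomarkers by result and measures their joint prognostic information in the same roughly 86 people, and the only stated correction does not deal with that selection. If the amount is given as ordinary explained variation and the gate is a two-sided 0.025 test, it is likely to be overstated for the selected set, materially so for true partial correlations of about 0.2 to 0.3 and little or not at all from 0.4 upwards. These sizes rest on the assumed gate, equal effects, error-free slopes and mutual correlations of 0 to 0.7, and they include ordinary overfitting. The documents do not support saying that the figure will certainly be inflated, or that it will be doubled in general. The point is minor: it leaves steps 1 and 2 and the primary objective untouched.

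**What to change.** State in step 5 that the joint model contains all five biomarker slopes regardless of their single-marker results. Report its explained variation as adjusted R², or corrected for optimism by bootstrap, with a confidence interval. If a model with selected biomarkers is also shown, repeat the selection inside each bootstrap sample so that the correction covers it.

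The cost is slightly more computing and, probably, a less favourable figure. No new data are needed.
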